### Additional data analysis

#### Economic evaluation

We will conduct a cost-effectiveness analysis of MTB relative to the control condition from a broad societal perspective.

Cost information: we propose two elements to the cost component of the cost-effectiveness analysis:Cost of MTB: this will include fixed costs associated with the resources required to run the service as well as variable costs associated with training, staffing and related consumables. We will calculate a bottom-up costing of the service and calculate a weighted cost per case based on the caseload of each practitionerCosts of the use of other resources: we will use a self-completed Service User and Support (SUS) questionnaire to collect other health and social care and out-of-pocket costs for clients in the MTB and the control group. The retrospective self-completed questionnaire will provide information on resources accessed during the last 6 months. The SUS will be completed at enrolment, 6 months after the baby is born by telephone and at each outcome assessment (infant age 1 and 2 years). Resource use will be costed using Personal Social Services Research Unit (PSSRU) and national datasets wherever possible

We will provide summary statistics of the costs for the MTB and the control group as well as a comparison of the total cost per patient to society of MTB compared to controls for the duration of the study.

Incremental cost-effectiveness ratio (ICER): the ICER is the mean cost per mother/child in the intervention minus the mean cost per patient in the control group divided by the mean incremental gain per mother/child in outcomes from the intervention compared to the controls. If an intervention has a lower cost to society and better outcomes it is considered dominant and likely to be adopted by a decision-maker if the evidence is satisfactory. If the intervention has higher cost to society but is associated with better outcomes the decision-maker needs adequate information to determine if they are willing to pay the additional cost per outcome gained.

We propose calculating a number of ICERs for MTB compared to controls and propose using the following outcomes in the denominator of the ICER for different analyses:Maternal sensitivityInfant QoL using the Warwick Child Health and Morbidity Profile [20, 78]Parental QoL using the EQ-5D, which is a brief questionnaire that measures generic health-related quality of life from the patient’s point of view. EQ-5D scores can be converted to preference-based utility scores that can be used to calculate quality-adjusted life years (QALYs) for use in cost-effectiveness analyses using an algorithm developed by Dolan [67]Mother-infant attachment

As the ICER does not easily allow for normal statistical tests we will use bootstrapping methods, replications of the statistic of interest by sampling with replacement from the original data, to calculate the confidence interval for the ICER. We will also use this data and the net-monetary benefit approach to calculate the probability that MTB is cost-effective compared to the control group for a number of values of willingness to pay per gain in outcome or the cost-effectiveness acceptability curve (CEAC) [19]. This provides more information to decision-makers to help them decide if the outcomes achieved as a result of the intervention are worth the additional cost.

Lifetime model: poor parent-child relationships, child abuse and neglect can have long-term negative impacts on children, their families and society. Poor parenting has repeatedly been identified as being associated with antisocial behaviour and severe behavioural problems [22, 23]. A long-term follow-up study of children with conduct disorder suggested that the cost of unresolved conduct disorders can exceed £1 million over an individual’s lifetime [2]. There are obviously further costs and benefits to realise as a result of preventing each case of child abuse and neglect. The ICERs proposed above do not capture the full lifetime costs and outcomes that may be realised as a result of MTB. As part of the project we would, therefore, aim to investigate developing a decision analytical model that uses information available from the evaluation, as well as published data sources, to determine the cost-effectiveness of MTB over the lifetime of the children.

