*Postponed child-bearing* will be assessed at each follow-up when mothers will be asked about their pregnancy status. The number of months from baseline to the next pregnancy will be used for analysis.

*Maternal mental health* will be measured with the Edinburgh Postnatal Depression Scale (EPDS: [46]) questionnaire which will be administered at baseline, year 1 and year 2. The EPDS is a 10-item questionnaire screening for postnatal depression. Mothers’ responses are on a scale of 0 to 3, and a score is calculated adding individual items. All three total scores from the questionnaire will be entered into the analysis, with change from baseline being the outcome of interest. EPDS is a well-validated measure of depression [47] that may be used within 8 weeks postpartum but has also been applied for depression screening during pregnancy [48].

*Child Quality of Life* will be assessed at year-1 and year-2 follow-ups with the Warwick Child Health and Morbidity Profile (WCHMP) questionnaire [49]. This consists in a 10-item survey where parents are asked to report on health and morbidity in infancy and childhood. The WCHMP has shown to be reliable and valid with low interobserver variation [49]. An incremental cost-effectiveness ratio (ICER) will be calculated and the two groups of mothers compared.

*Health and social care resource use* will be collected throughout the study using the Service Use and Supports Questionnaire (SUS) [50]. This is a self-report questionnaire administered at baseline and every subsequent follow-up, i.e. 6 months, year 1, 18 months and year 2. Mothers are asked to note whether they had any input from professionals and voluntary agencies in the previous 6 months, in four areas: (1) health services, (2) mental health services, (3) support services and (4) child care services. Parents are also asked to note down the single most helpful service they have accessed over the previous 6 months. Costs are applied to service use at each time point. Total costs per patient will be calculated from the total across all follow-up points and adjusted for by baseline values. Unit costs will be obtained from the Personal Social Services Research Unit’s (PSSRU) nationally published reference costs and published studies.

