Child cognitive and language development	Bayley Scales of Infant and Toddler Development Scales, third edition (Bayley-III). Individual administration. Continuous scales produce scores. Validated for UK and Ireland use [43]	Year 2
Behavioural problems	Child Behaviour Checklist (CBCL).100-item questionnaire. Responses are on a scale of 0 to 2. Validated for international use [45]	Year 2
Postponed child-bearing	Mother asked about her pregnancy status. Number of months from baseline to the next pregnancy used for analyses. Extensive use with similar studies (e.g. [1])	6 months, year 1, 18 months and year 2
Maternal mental health	Edinburgh Postnatal Depression (EPDS).10-item questionnaire. Responses are on a scale of 0 to 3. Validated measure of depression [47]	Baseline, year 1 and year 2
Child quality of life (QoL)	Warwick Child Health and Morbidity Profile (WCHMP). 10-items survey. An incremental cost-effectiveness ratio (ICER) calculated. Validated with low interobserver variation [49]	Year 1 and year 2
Health and social care resource use	Service Use and Support (SUS). 36-item questionnaire. Cost of services calculated with the Personal Social Services Research Unit (PSSRU). Extensive use in clinical studies (e.g. [80])	Baseline, 6 months, year 1, 18 months and year 2
Additional outcome measures		
Measurement of temperament	Infant Behaviour Questionnaire Revised (IBQ-R). 37-item questionnaire. Responses are on a scale of 1 to 7. Good internal consistency reliability and convergent validity [52]	Year 1
Sensitivity scale	Maternal and paternal Sense of Mastery (MSM). 7-item questionnaire. Responses are on a 7-item scale (agreement to disagreement). Extensive use with similar sample of young women [53]	Baseline, year 1 and year 2
Social support	Norbeck Social Support questionnaire (NSSQ). 9-item questionnaire. Responses are on a scale of 0 to 4. Validity and reliability on all measures [57]	Baseline, year 1 and year 2
Infant health outcome	Health records reviewed at the end of the study and data collected on different issues, including hospitalisation and Social Services’ referrals. Extensive use with similar studies (e.g. [1])	Year 1 and year 2
Parental representation of their child	Parent Development Interview – Revised (PDI). 20-item interview. Scores are on a scale of 1 to 9. Validity shows links to adult attachment and child attachment [29, 32, 58, 59]	Year 1

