### Planned intervention

#### Minding the Baby®

MTB is a home-visiting programme that helps vulnerable or high-risk first-time mothers aged 14–25. The programme has been developed by the Yale Child Study Centre and the Yale School of Nursing, with the main focus being on the parent-child relationship. The MTB programme is delivered by an interdisciplinary MTB team of highly skilled practitioners, a nurse or health visitor experienced in parental, perinatal and paediatric roles and a social worker or other suitably trained practitioner trained in mental health assessment and intervention.

Mothers are visited weekly at home from the third trimester until the child’s first birthday and then fortnightly until their second birthday. The two MTB practitioners’ visits are alternated weekly. Visits can be increased as required, particularly in times of crisis.

The health practitioner’s role will focus primarily, but not exclusively, on the following:

Parental care and health educationPractitioners provide ongoing support and information about maternal and infant nutrition and healthy child growth and development, including fetal and postnatal brain development. Support is given regarding the prevention of premature birth and planning for labour and delivery. Practitioners also help pregnant women to begin to anticipate and imagine life with a newborn, what its needs might be, and how one interacts and communicates with a young infant. Practical and educational support is given to women pre and postnatally regarding breast feeding

Child health and developmentThe health practitioners undertake routine assessments of the child’s physical, cognitive and social development and provide advice and guidance about the child health, including advice regarding the identification and treatment of illnesses. Practitioners also provide information and advice about a safe environment for the child to reduce incidents of injury. Finally, practitioners provide anticipatory and ongoing guidance about parenting of young infants and toddlers

Mother’s healthPractitioners are trained to help women think about safe sex and future family planning, provide support and information regarding healthy lifestyles, including smoking cessation support and healthy nutrition and exercise. Practitioners also assist mothers in obtaining support when they experience physical or mental health difficulties (e.g. via primary care) or have ongoing problems with stress

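### The economic section drops the 18-month service-use questionnaire listed elsewhere, and with six-month recall neither schedule covers the interval from enrolment to birth

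*Protocol article*

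**What the plan says.** The protocol article gives two schedules for the Service Use and Supports Questionnaire (SUS).

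- **Economic evaluation:** "The SUS will be completed at enrolment, 6 months after the baby is born by telephone and at each outcome assessment", the outcome assessments being at infant ages 1 and 2 years. There is no 18-month wave.
- **Secondary outcomes** (health and social care resource use): "administered at baseline and every subsequent follow-up, i.e. 6 months, year 1, 18 months and year 2". The matching row of Table 1 agrees: "Baseline, 6 months, year 1, 18 months and year 2". Table 2 also marks questionnaires at 18 months, with a 15-minute slot.

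Both sections fix the look-back at six months. The economic section says "The retrospective self-completed questionnaire will provide information on resources accessed during the last 6 months"; the outcome section says "Mothers are asked to note whether they had any input from professionals and voluntary agencies in the previous 6 months".

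The outcome section forms total cost per participant by adding up the follow-up waves and adjusting for baseline. The economic section promises a comparison of total societal cost over the whole study. MTB itself is costed separately, bottom-up, and its delivery starts before birth: "Mothers are visited weekly at home from the third trimester until the child’s first birthday". Baseline is antenatal (Abstract), but no gestational age at baseline is stated.

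**The concern.** A wave with a six-month look-back captures only the six months before it. When consecutive waves lie further apart, the time between is never asked about, and a total built by adding up waves omits it.

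This happens in two places. Without the 18-month wave, the year between the first and second birthdays is only half covered. And because the first follow-up wave is six months after birth, it reaches back no further than birth, while the baseline wave looks back from enrolment. Nothing covers enrolment to birth. Adjusting for baseline does not help, since baseline describes the months before enrolment.

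The omission need not cancel between arms. MTB practitioners signpost mothers to other services and help them obtain support, and MTB may also replace some usual care. In the last trimester MTB's own cost is counted while the services it may displace or prompt are not. QALYs are an area under the curve from a baseline EQ-5D, so that ratio's denominator includes antenatal time that the SUS part of the numerator leaves out. Cost-effectiveness is named as a key secondary aim (Aim 3).

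**Working it through.** The protocol states no coverage figure, so there is none to reproduce. The check is interval arithmetic.

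**Inputs from the document**
- Look-back: 6 months (Secondary outcomes; Economic evaluation).
- Postnatal waves, economic section: 6, 12 and 24 months.
- Postnatal waves, Secondary outcomes and Table 1: 6, 12, 18 and 24 months.
- The first follow-up wave is counted from birth (Economic evaluation); the year-1 and year-2 assessments fall around the birthdays (Abstract).

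**Assumptions**
- Birth at 40 weeks, and every wave on time.
- Gestation at enrolment of 20 to 28 weeks, with later values shown. The 20-week scan is the usual recruitment point; 28 weeks approximates the start of the third trimester.
- 365.25 / 12 / 7 = 4.348 weeks per month.

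**Step 1: postnatal coverage (needs no gestational age)**
- With the 18-month wave: 0–6, 6–12, 12–18 and 18–24 months are covered. Gap 0 of 24 months.
- Without it: 0–6, 6–12 and 18–24 months are covered. Gap 6 / 24 = 25%.

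**Step 2: enrolment to birth**

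Let g = (40 − week of enrolment) / 4.348 months and T = 24 + g. The uncovered share is g / T with the 18-month wave and (6 + g) / T without it.

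| Week of enrolment (assumed) | g (months) | T (months) | With 18-month wave | Without 18-month wave |
|---|---|---|---|---|
| 20 | 4.60 | 28.60 | 4.60 / 28.60 = 16.1% | 10.60 / 28.60 = 37.1% |
| 28 | 2.76 | 26.76 | 2.76 / 26.76 = 10.3% | 8.76 / 26.76 = 32.7% |
| 34 | 1.38 | 25.38 | 1.38 / 25.38 = 5.4% | 7.38 / 25.38 = 29.1% |
| 38 | 0.46 | 24.46 | 0.46 / 24.46 = 1.9% | 6.46 / 24.46 = 26.4% |

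**Step 3: does the starting point of the clock matter?**
- If only the 6-month wave is counted from allocation, the gap moves to just before the year-1 look-back but keeps its length g, so the shares are unchanged.
- If every wave is counted from allocation, the gaps are 0 of 24 months with the 18-month wave and 6 of 24 (25%) without it. That reading conflicts with the economic section, which times the first wave from birth, and with the assessments around the birthdays.

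**Step 4: recall length if the 6-month call reaches back to enrolment**

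6 + 2.76 = 8.8 months to 6 + 4.60 = 10.6 months, so about 9 to 11 months.

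**The case against.** The best defence is that the missing 18-month wave is a slip of drafting. The outcome section, which also defines total cost, includes it; Table 1 repeats it; Table 2 reserves time for it. Only the economic section differs, and on the better-supported schedule all 24 postnatal months are covered. This stands: the 18-month point is a contradiction to reconcile, not a proven hole in data collection.

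The antenatal share also depends on a date that the article does not give. The 20-week scan usually yields only agreement to be contacted; written consent and baseline follow at a later home visit, and self-referral or professional referral has no stated gestation limit. Enrolment at 20 weeks is therefore an extreme, and 10% is not a floor. This stands too.

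A reader might infer that 10% to 37% of total costs are lost. The document does not support that. The range joins two alternative schedules, rests on the assumed enrolment week, and measures time outside SUS recall rather than money. MTB delivery is costed separately, and the infant record review (Additional outcome measures) supplies birth outcomes, hospital and A&E visits and Social Services referrals with unit costs, whatever the SUS recall. A reader might also infer that the gap favours one arm. It applies to both randomised arms, and only a between-arm difference in other service use during it would matter. Neither the size nor the sign of that difference can be derived from the article.

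Lastly, a condensed article may leave questionnaire wording to a fuller document. That would excuse silence, but here the look-back and the wave times are both stated and do not fit together.

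**Conclusion.** The point holds in this form. The economic section contradicts the Secondary outcomes section, Table 1 and Table 2 on the 18-month SUS. If it is followed, 6 of 24 postnatal months (25%) lie outside SUS recall. Under either schedule, enrolment to birth lies outside it as well: about 2.8 to 4.6 months, or 10% to 16% of follow-up time, for enrolment at 28 to 20 weeks, falling to about 2% at 38 weeks. The 25% needs only the stated wave times and look-back; the antenatal figures rest on the assumed enrolment week, birth at 40 weeks and a first follow-up wave timed from birth.

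These are shares of follow-up time. The loss as a share of total cost cannot be computed, and infant costs are partly protected by the record review. Incremental cost may be biased because third-trimester MTB visits are costed while other services in those weeks are not, but the direction is unknown. Action is warranted because a total over the whole study is promised and service use that was never asked about is hard to recover later.

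**What to change.** 1. Bring the Economic evaluation section into line with the five-wave schedule: baseline, 6 months, year 1, 18 months and year 2. The 18-month contact is already planned, so this is a correction of text.
2. Change the recall instruction to 'since enrolment' at the 6-month call and to 'since your last questionnaire' at later waves.
3. Recruitment began in April 2014, so some mothers may already have passed the 6-month call. Flag those who answered under the six-month wording and handle them in a sensitivity analysis. Maternal records could supply their enrolment-to-birth contacts only where the consent described under Scope of consent to participation allows it. The planned infant record review is not a substitute, as it is not described as covering the mother's antenatal service use.

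The cost is one longer recall period of about 9 to 11 months, with more recall error; different recall windows for earlier and later participants; and an amendment needing ethics committee and local R&D approval. Any use of maternal records would be new data collection.

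If the recall wording is not changed, state that costs other than MTB cover birth to 24 months only, and add a sensitivity analysis in which the MTB cost and the QALY period are restricted to the same window.

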### Data monitoring

#### Data monitoring

The Trial Steering Committee (TSC) will take the role of monitoring trial safety and data monitoring. The statistician will review the data on an ongoing basis, including any adverse event records, and report this to the TSC. Detailed reports will be prepared by the TSC statistician to monitor safety/adverse event data, recruitment and dropout rates. The formal statistical interim analysis of the primary outcome will be reported to the TSC after the end of the first outcome phase.

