### Randomisation

Eligible consenting participants will be randomised on a 1:1 basis by the randomisation centre (supervised by [name]) at a separate site, who will manage randomisation. Monitoring of data quality and integrity will be done separately by [name], study statistician. Together they will act as DMEC and will have power to break confidential ID codes should ethical concerns arise. A computer-generated adaptive minimisation algorithm [72] that incorporates a random element will be used with the following balancing factors: treatment centre, maternal age (below 20 versus 20 years or older) and current depressive symptomatology (< 10 versus ≥ 10 on the EPDS). These minimisation factors have been selected because previous research has shown that these factors are associated with poorer outcomes on some of our dependent measures or are highly plausible treatment modifiers. Once a family has been approached and has consented to take part, anonymised screening data will be sent to the randomisation centre by the trial coordinator. The randomisation centre will send the results of the randomisation to the local clinical manager within 72 h, ensuring that the research team is fully blind to the condition that the family is allocated to. Participants will be informed about their group allocation, as blinding to a psychosocial treatment of this nature is not possible. The outcome assessors will be blind to the participants’ allocation. During training, all research assistants (RAs) will be briefed regarding the importance of blindness to condition and they will record any instances where the participating family discloses its condition inadvertently, so that the impact of this can be examined in the data analysis. Coding of the primary outcome will be done independently from video recordings by raters who have no contact with the participants.

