### Data transfer

In the study, all participant data as outlined previously in this protocol will be collected in accordance with the participant Consent Form and Participant Information Sheet. All participant data will be appropriately sent to [name] for statistical analysis and UCL will act as the data controller of such data for the study. [name] will be responsible for the processing, storage and disposal of all participant data in accordance with all applicable legal and regulatory requirements, including the Data Protection Act 1998 and any amendments thereto.

Data will be stored on a secure server dedicated exclusively to this project that has encrypted access. Only the research team will have access to the data and to information identifying participants. Research data and personally identifying data will be stored in separate, web-accessible, secure databases. All research data will be stored in locked filing cabinets in each site. Similarly, Consent Forms will be stored separately from the research data in locked filing cabinets in each site. Risks to subject confidentiality will be minimised by adopting suitable data storage procedures in accordance with best practice guidelines and in accordance with the Data Protection Act. Subjects will be assigned ID numbers. The master ID list that links subject names with ID numbers will be kept on a highly secure password-protected server. All information concerning allocation to condition (TAU or MTB) will be held securely by the randomisation centre. Clinical records and other relevant clinical information regarding participants in the MTB arm will be held by the NSPCC, following their standard governance protocols.

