### Data analysis

The primary outcome, maternal sensitivity, is an average of several ordinal scores and is typically found to be approximately normally distributed. The primary analysis will be a regression analysis testing group differences in mean sensitivity at year 1 after adjustment for baseline characteristics. Clustering by therapist and site will be allowed for by computing robust standard errors [74]. Continuously distributed secondary outcomes will be treated in the same manner. The risk of child protection intervention will be described using the Kaplan-Meier method and summarised by the proportions of children with child protection intervention over 2 years period of observation. The primary analysis for this outcome will be Cox regression, adjusting for key baseline characteristics.

Where there are missing data, these will be evaluated either by multiple imputation or a sensitivity analysis determined by the pattern of missing data. In doing so, we will follow the procedures and guidance outlined by Sterne and colleagues [75]. Mediational analyses of change mechanisms (e.g. age 12 months’ maternal sensitivity-mediating treatment effects on attachment at age 2 years) will be tested using bootstrap methods described by MacKinnon and Dwyer [76] and Preacher and Hayes [77].

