#### Trial Steering Committee

A TSC will be used to monitor the progress of the project and advise the research team on matters arising during subsequent phases of the study. The TSC will meet 6-monthly and perhaps more regularly during the preparatory and final stages of the formal evaluation. The group will be made up of representatives from the NSPCC, researchers, a statistician, service users and/or carers and representatives of professional/provider organisations, including a link person from at least two local clinical teams.

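### The interim result on the primary outcome goes to a steering committee that includes the NSPCC, researchers and clinical-team members while home visits and part of the year-2 assessments are still under way

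*Protocol article*

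**What the plan says.** The Data monitoring section gives oversight to one body: "The Trial Steering Committee (TSC) will take the role of monitoring trial safety and data monitoring". It then announces an interim look: "The formal statistical interim analysis of the primary outcome will be reported to the TSC after the end of the first outcome phase".

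The Trial Steering Committee section describes the members: "The group will be made up of representatives from the NSPCC, researchers, a statistician, service users and/or carers and representatives of professional/provider organisations". The same sentence goes on to bring in people from the local services, "including a link person from at least two local clinical teams". One task of the committee is to "advise the research team on matters arising during subsequent phases of the study".

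The NSPCC is not a bystander. The Background overview names it as initiating the study with its university partners, and under Data transfer: "Clinical records and other relevant clinical information regarding participants in the MTB arm will be held by the NSPCC".

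The Randomisation section undertakes to keep the research team blind to each family's allocation. It also sets up a second body, formed by the randomisation supervisor and the study statistician: "Together they will act as DMEC and will have power to break confidential ID codes should ethical concerns arise". The Data monitoring section does not mention that body.

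**The concern.** The recipient, its membership and the timing are all fixed in the article, so this is a stated routing rule and not a detail left to another document. Read together, the sections put a primary-outcome result in front of people who run, advise or deliver parts of the trial before follow-up is finished.

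Knowing the direction of the year-1 effect could change how intensively the programme is delivered, how hard each site works to retain families, and how year-2 measures are administered or answered. Bias that enters during follow-up cannot be removed in the analysis. The arrangement also sits badly with the effort made elsewhere to keep researchers blind, and it leaves unclear which body is meant to see comparative data.

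**Working it through.** **1. Is the trial still running at the interim?** Outcomes are assessed around the first and second birthdays (Abstract; Primary outcome), so the first outcome phase is the year-1 assessment. Home visits continue fortnightly to the second birthday (Planned intervention). Treatment and year-2 collection therefore overlap the interim for every child then between one and two years old.

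**2. How much of year 2 is exposed?** The article does not say, but a rough size follows from its dates.
- Recruitment began in April 2014 and was still open at the time of writing (Trial status). The article cites a protocol version dated 11 January 2016 (Ethical considerations), so entry spans at least about 21 months.
- Year 1 and year 2 are 12 months apart.
- Assume that the phase ends with the last child's year-1 assessment and that entry is even over T months. The share of year-2 assessments still outstanding is then 12/T.
- T = 21 gives 12/21 = 57%; T = 24 gives 50%; T = 30 gives 40%.

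So part of the year-2 data is exposed, possibly about half, but not all of it.

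**3. Which outcomes are open to influence?**
- Year-2 maternal sensitivity is the best protected: it is coded from video by raters with no participant contact (Randomisation).
- The Attachment Q-Set is sorted by the researcher who observed the family.
- The CBCL is reported by the parent.
- The EPDS is completed by the mother, who knows her allocation.

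**4. Is any alpha set aside?** The Power analysis gives the only alpha, .05 for one single-df test, with N = 129.
- f² = (.20 − .15)/(1 − .20) = .0625.
- Noncentral F test: numerator df 1, denominator df N − k − 1 with k = 4 or 5, noncentrality f²N, power 80%.
- Result: N = 128, against the stated 129.

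The stated figure is reproduced to within one participant with the whole .05 spent on one test, so the sample size reserves nothing for an interim.

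**5. Does that inflate type I error?** It depends on what the final analysis is.
- *Year 1 only.* Data analysis describes the primary analysis as "testing group differences in mean sensitivity at year 1". The interim is then the primary comparison itself. There is one test, and alpha stays .05.
- *Both years.* The Primary outcome section puts both time points into the primary analysis. Take the final statistic as the average of the two years, with equal variances and complete data. Its correlation with the year-1 statistic is ρ = √((1 + r)/2), where r is the between-year correlation, which is assumed because the article gives none. If both looks were tested at two-sided .05, overall error is 1 − P(|Z₁| < 1.96, |Z₂| < 1.96):

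| r (assumed) | ρ | Overall type I error |
|---|---|---|
| 0.3 | 0.806 | 0.078 |
| 0.5 | 0.866 | 0.073 |
| 0.7 | 0.922 | 0.068 |

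These figures apply only if the interim could lead to an efficacy claim or an early stop. The article states neither.

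**The case against.** The best defence is that a group-level result reveals no family's allocation, so the blinding undertaking is not literally broken. Assessors are to be blind, inadvertent disclosures are recorded, and the primary outcome is coded from video by people who never meet the family. Mothers already know their arm, and practitioners must. The article condenses a longer protocol and does not say that the committee sees unmasked results by arm; closed sessions, masking and boundaries may be set out elsewhere. Nor does it say that the link persons come from teams delivering the programme.

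Much of this stands and limits the point. It does not remove it. A formal analysis of the primary outcome is naturally a treatment comparison, the listed members include researchers and the NSPCC whoever the link persons are, and the video safeguard does not extend to the Attachment Q-Set, CBCL or EPDS.

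Three stronger readings are tempting but not supported:
- *Error approaching 10%.* Testing year 1 and then year 2 alone, each at .05, would give 8.4-9.5% for correlations of 0.7-0.3. Neither the Primary outcome section nor Data analysis contains a stand-alone year-2 primary test.
- *All year-2 outcomes still to come.* Staggered entry over at least 21 months means that the earliest children would already have passed year 2.
- *The DMEC is bypassed.* The Abbreviations expand it as a data management and ethics committee, and its stated power is to break ID codes for ethical concerns. It is given no interim efficacy role. The two descriptions of monitoring need reconciling, but no assigned function is shown to be skipped.

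**Conclusion.** The point holds on access to comparative results. As written, the article sends an interim analysis of the primary outcome to a committee that includes the NSPCC, researchers and clinical-team link persons, and that advises the research team, while home visits and at least part of the year-2 assessments continue. That the result is comparative and that collection is still open are both inferences, but firm ones from the wording and the visit schedule. The size of any resulting bias cannot be computed from the article. The share of year-2 assessments exposed would be about 40-57% for even entry over 30 to 21 months.

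Type I error is secondary and conditional: no inflation if year 1 alone is primary; about 6.8-7.8% if the final analysis averages both years, the between-year correlation is 0.7-0.3, and the interim can support a claim at .05. The absence of a stated boundary is not itself a finding, since an analysis plan may supply one.

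**What to change.** - Limit reports to the Trial Steering Committee to pooled recruitment, dropout and safety data.
- Hold the year-1 between-arm comparison until year-2 data collection is complete and the database locked. If a comparative look is kept, give it only in closed session to people with no part in delivery or assessment.
- Reconcile the Randomisation, Data monitoring and Trial Steering Committee sections so that one named body is responsible for comparative data.
- State that the interim supports no efficacy claim and no early stop. This also settles the type I error question under either reading of the primary time point.

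Deferring the comparison needs only a change of wording. Keeping a comparative look costs more: a closed-report route and suitable members must be found, and the two-person DMEC would need review because one member is the study statistician. In either case the team learns the year-1 results later.
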